## Abstract

**Background:**

Smoking and physical inactivity are major risk factors for heart disease. Linking strategies that promote improvements in fitness and assist quitting smoking has potential to address both these risk factors simultaneously. The objective of this study is to compare the effects of two exercise interventions (high intensity interval training (HIIT) and lifestyle physical activity) on smoking cessation in female smokers.

**Method/design:**

This study will use a randomised controlled trial design. Participants: Women aged 18–55 years who smoke ≥ 5 cigarettes/day, and want to quit smoking. Intervention: all participants will receive usual care for quitting smoking. Group 1 - will complete two gym-based supervised HIIT sessions/week and one home-based HIIT session/week. At each training session participants will be asked to complete four 4-min (4 **×** 4 min) intervals at approximately 90 % of maximum heart rate interspersed with 3- min recovery periods. Group 2 - participants will receive a resource pack and pedometer, and will be asked to use the 10,000 steps log book to record steps and other physical activities. The aim will be to increase daily steps to 10,000 steps/day. Analysis will be intention to treat and measures will include smoking cessation, withdrawal and cravings, fitness, physical activity, and well-being.

**Discussion:**

The study builds on previous research suggesting that exercise intensity may influence the efficacy of exercise as a smoking cessation intervention. The hypothesis is that HIIT will improve fitness and assist women to quit smoking.

**Australian New Zealand Clinical Trials Registry:**

ACTRN12614001255673 (Registration date 02/12/2014)

## Background

Tobacco smoking is a major cause of cardiovascular disease, chronic obstructive pulmonary disease and many cancers. In women, research has shown that between the ages of 18 to 55 years, the largest population risk for heart disease is attributable to smoking (particularly in young women) and physical inactivity [1]. Despite steady declines in smoking prevalence over the past thirty years, in 2011–12, 16 % (1.4 million) of Australian women aged 18 years and over smoked daily. The 2009 National Preventative Health Strategy calls for a target of 10 % or less for smoking prevalence by 2020. This target will not be reached unless rates of cessation substantially increase [2]. More than half of all smokers want to quit [3], but many struggle to achieve abstinence, and relapse is common, with only 5 % of smokers who quit without any assistance still abstinent at 6 months [4]. As many smokers cite ‘wanting to get fit’ as a motivation for quitting [5], linking strategies that will simultaneously promote improvement in fitness and assist quitting has the potential to change both behaviours simultaneously [6].

There is evidence for a positive effect of exercise when quitting smoking [7], with physical activity (PA) reducing cigarette cravings and withdrawal symptoms [8]. However, the evidence for the efficacy of PA as an aid to quitting smoking is mixed. A recent systematic review of 15 randomised controlled trials highlighted insufficient exercise intensity as a potential limitation of interventions tested in previous trials which did not improve smoking abstinence rates [7].

High Intensity Interval Training (HIIT) could overcome the potential limitation of insufficient intensity, by providing alternating short bursts of high intensity exercise with recovery periods of light exercise. HIIT provides rapid physiological adaptations, as indicated by improvements in maximal oxygen uptake (VO_2_max), anaerobic threshold and stroke volume [9, 10].

### Aims

The aims of this project are to: (1) compare the effects of two exercise interventions (HIIT and a ’10,000 steps’ pedometer based intervention) combined with usual care smoking cessation support, on cessation rates in female smokers who wish to quit; (2) assess the effects of HIIT and 10,000 steps interventions on weight change and (3) assess whether improvements in fitness, vitality and intrinsic motivation are mediators of the relationship between activity and smoking cessation.

## Methods

### Design, participants and recruitment

The study has received ethical approval from the Medical Research Ethics Committee of The University of Queensland (#2014001266). This study will use a two group randomised controlled trial design. Inclusion and exclusion criteria are provided in Table 1. Women aged 18–55, smoking at least five cigarettes a day, and who identify as being willing and ready to make a quit attempt will be recruited. Recruitment will be from the local population using radio and print media, advertising, and through collaborations with local health services. A phone number, study email and website will be available for interested participants to contact the research team. A member of the research team will follow-up with a phone call to screen for eligibility, explain the main requirements of the study, and send the Participant Information and Consent Form (PICF). If women wish to participate they will be invited to attend a screening/baseline visit (Fig. 1) and sign the PICF before any data are collected.

**Table 1 Tab1:** Inclusion/exclusion criteria

Inclusion criteria	Exclusion criteria
Women aged 18 to 55 years	Currently using pharmacological quit smoking aids
Currently smoking at least 5 cigarettes per day	Medical problems that increase risk of adverse events during exercise (including unstable angina, pulmonary disease, uncontrolled hypertension, cardiomyopathty, orthopaedic or neurological limitations)
Desire to quit smoking	Planned surgery during research period
Willing to attend the gym twice weekly if allocated to HIIT intervention group	Current or planned pregnancy
	Drug or alcohol abuse

**Fig. 1 Fig1:**
[figure not shown]
Flow of study

**Fig. 2 Fig2:**
[figure not shown]
Example of a 35 min 4 × 4 HIIT session

### Randomisation, allocation and concealment

Participants who complete baseline measures will be randomised into one of two groups: 1) HIIT or 2) 10,000 steps (Fig. 1). Each participant will be randomized into one of the two study conditions according to an allocation sequence generated by a computer program and concealed within sealed opaque sequentially numbered envelopes. Analyses will adjust for any baseline differences, consistent with standard procedures. Participants will be allocated to conditions one-at-a-time, allowing for a “rolling start” to the intervention.

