### Data collection

Participants will be assessed on three occasions: at baseline, week 13 and week 26 (see Fig. 1). Cigarettes per day will be measured weekly. Withdrawal symptoms, cigarette cravings and feelings of stress, will be monitored during the intervention. See Table 2 for full list of measures, and measurement time-points. Exercise and fitness measures will be completed by research staff whom will be blinded to participant group allocation.

**Table 2 Tab2:** Timeline for data collection

	Measurement time-point					
Measures	Baseline	Week 2	Week 4	Week 8	Week 13	Week 26
Cigarettes per day (weekly)						
Smoking cessation					X	X
Withdrawal symptoms	X	X	X	X	X	X
Cigarette cravings	X	X	X	X	X	X
Cigarette dependence	X				X	X
Subjective stress	X		X	X	X	X
Saliva cotinine	X				X	X
Cardiorespiratory fitness	X				X	X
Lung function	X				X	X
Body composition	X				X	X
Physical activity	X				X	X
Well-being	X				X	X
Motivation	X				X	X
Demographic information	X				X	X

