### Data analysis

The aim of this study is to obtain data on the effects of HIIT training on smoking cessation and intermediate outcomes, such as cigarette cravings and withdrawal symptoms. Using effect size estimates based on results of a previous study using vigorous PA for smoking cessation in women (i.e. OR = 2.09, [18]), adopting a two tailed alpha level of 0.05 and power 0.80, a sample size of 100 will be required. Based on funding and time constraints, the study aims to recruit 50 participants per group. Descriptive statistics will be used to summarize the characteristics of participants in each group, and to describe those who successfully quit. Yates’ corrected Chi-squared test will be used to analyse the difference in the proportions who quit in each group, and changes in categorical (e.g. smoking abstinence) and continuous (e.g. number of cigarettes smoked) variables will be assessed using generalised linear modeling.

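### Covariates are to be chosen by observed baseline differences, and the plan does not say whether the adjusted or the unadjusted analysis of quitting is the main one

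*Protocol article*

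**What the plan says.** The section on randomisation, allocation and concealment states that participants are allocated "according to an allocation sequence generated by a computer program and concealed within sealed opaque sequentially numbered envelopes". It mentions no stratification. It then says: "Analyses will adjust for any baseline differences, consistent with standard procedures". Neither a list of covariates nor a definition of a difference is given.

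The Data analysis section says that a Yates "corrected Chi-squared test will be used to analyse the difference in the proportions who quit in each group". The same sentence adds that "changes in categorical (e.g. smoking abstinence) and continuous (e.g. number of cigarettes smoked) variables will be assessed using generalised linear modeling". Smoking abstinence therefore falls under both methods. The section names no covariates, does not rank the two analyses, and does not refer back to the adjustment rule.

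On baseline data, the Data collection section says: "See Table 2 for full list of measures, and measurement time-points". Twelve rows of that table carry a baseline mark.

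**The concern.** With a concealed, computer-generated sequence, a baseline difference between the groups is a chance event. Its size does not show whether the variable predicts quitting. A rule that adjusts for whatever differs omits strong predictors that happen to be balanced and admits weak ones that are not. The set of covariates, and with it the odds ratio being estimated, is known only once the data are in.

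The wording is also open-ended, because any difference could qualify. Several rows of Table 2 hold more than one variable: the well-being measure alone has two summary scores and eight subscales, and the demographic survey covers age, education, occupation, income and two kinds of history.

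Two things are at stake for Aim 1, the comparison of cessation rates. One is precision, which prespecified adjustment could gain from data already collected. The other is that the result to be put first (adjusted or not, and for what) is not fixed before the data are seen.

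**Working it through.** **Inputs from the protocol article.** 50 per group ("the study aims to recruit 50 participants per group"), odds ratio 2.09, two-sided alpha 0.05 (all Data analysis), and 12 measures marked at baseline (Table 2). No control quit rate is stated. The only rate in the text, "only 5 % of smokers who quit without any assistance still abstinent at 6 months" (Background), refers to unassisted quitters and is not the design assumption.

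**The plan's own figure.** The plan gives no figure for the adjustment rule. Its sample size statement ("adopting a two tailed alpha level of 0.05 and power 0.80, a sample size of 100 will be required") supplies only the group size here. That figure does not reproduce from an odds ratio of 2.09: the smallest requirement at any control rate is 117 per group, or 234 in total. This is a separate matter and nothing below depends on it, but it explains why the powers in step 3 are low.

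**Step 1: how often chance produces a difference.** Assume 12 independent measures, each tested at 5%. P(at least one) = 1 − 0.95^12 = 0.46. The simulation in step 3 gave 45% to 48%. The expected number of flagged measures is 12 × 0.05 = 0.6.

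**Step 2: how many quits there are to model.** Treated rate = odds × 2.09 / (1 + odds × 2.09), where odds = control rate / (1 − control rate).
- Control rate 10% (assumed): 0.1111 × 2.09 = 0.2322, so the treated rate is 0.2322/1.2322 = 0.188. Quits = 50 × (0.10 + 0.188) = 14.4.
- Control rate 20% (assumed): 0.25 × 2.09 = 0.5225, so the treated rate is 0.5225/1.5225 = 0.343. Quits = 50 × (0.20 + 0.343) = 27.2.

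If all 12 measures entered as single terms alongside group, that is 13 terms: 14.4/13 = 1.1 to 27.2/13 = 2.1 quits per term. With group and one covariate it is 14.4/2 = 7.2 to 27.2/2 = 13.6.

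**Step 3: power and type I error for quitting.** Simulation with 4,000 runs per setting and 50 per group. There were 12 independent normal covariates, two of them prognostic with log odds ratio 0.3, 0.7 or 1.0 per SD (assumed). The control quit rate at average covariate values was 1/(1 + e^1.1) = 25% (assumed). The triggered rule adjusted for every covariate with baseline p < 0.05.

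| Odds ratio 2.09 | Weak (0.3) | Moderate (0.7) | Strong (1.0) |
|---|---|---|---|
| Prespecified adjustment | 37.8% | 34.1% | 32.2% |
| Triggered adjustment | 36.6% | 27.7% | 25.2% |
| Unadjusted logistic | 36.8% | 28.6% | 26.0% |
| Yates chi-squared | 30.1% | 23.5% | 19.9% |

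The loss of the triggered rule against prespecified adjustment is 37.8 − 36.6 = 1.2, 34.1 − 27.7 = 6.4 and 32.2 − 25.2 = 7.0 points. The standard error of one entry near 30% is √(0.3 × 0.7/4000) = 0.7 points, so the loss with weak covariates is barely distinguishable from simulation noise.

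With no true effect, the triggered rule rejected in 4.7%, 3.8% and 4.2% of runs.

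**The case against.** The strongest defence is that an article condenses the full plan, and that covariates and the rank of analyses are usually settled in the statistical analysis plan. For a missing covariate list that would be a full answer. It does not cover this sentence, which states a rule: a later plan that fixed covariates regardless of balance would contradict it.

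Other objections stand and limit the point.

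- A reader might infer that the plan contains two incompatible analyses of quitting. It does not. A crude test beside a model is common practice, and the generalised linear model named for abstinence can carry covariates. What is unstated is the role of each.
- A reader might infer a large loss of power. For a continuous outcome, with an assumed effect of 0.5 SD and one covariate correlated 0.5 or 0.7 with it, triggered adjustment gives 72% against 82% or 94% when always adjusting. Those inputs are not in the protocol and do not carry over to a binary quit outcome. Against an unadjusted logistic model the triggered rule loses under 1 point at an odds ratio of 2.09, and it has more power than the Yates test that the plan names.
- A reader might infer more false positives. The mechanical rule shows none. Picking covariates after seeing outcomes was not simulated, and nothing in the protocol says that this is intended.
- The 46% needs a 5% trigger and independent measures. The plan states no trigger, and dependence, cotinine, cravings and withdrawal are plainly related.
- Overfitting arises only under the open-ended reading. A 5% trigger would add 0.6 covariates on average.

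**Conclusion.** The point holds in limited form. The protocol article fixes a data-driven rule for choosing covariates where a prespecified one would be better and would cost nothing. It also leaves open whether the adjusted model or the unadjusted test is the main analysis of quitting.

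The demonstrated cost for quitting is about 1 to 7 percentage points of power against prespecified adjustment, at 50 per group and an odds ratio of 2.09. This rests on assumed covariate strengths and an assumed control rate of about 25%. Overfitting becomes a concern if the covariate set is truly open-ended, given 14 to 27 expected quits at assumed control rates of 10% to 20%. Type I error is not inflated by the rule itself. The flaw does not invalidate the trial, but it should be corrected before outcomes are compared between groups.

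**What to change.** Replace the adjustment sentence in the randomisation section with:

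> Analyses will adjust for a small set of prognostic baseline covariates fixed in advance, regardless of observed balance (for example baseline FTND for abstinence, and the baseline value of the outcome for continuous measures). No covariate will be added because of a baseline difference.

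In the Data analysis section, state that the adjusted generalised linear (logistic) model is the main analysis of quitting and that the Yates chi-squared test is the unadjusted supporting analysis.

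FTND is offered as an example because Table 2 marks dependence at baseline. The protocol does not show it to be the best predictor, and the choice is the trial team's. Cigarettes per day is another candidate. Its row in Table 2 has no baseline mark, although eligibility requires the number to be known, so the team should confirm that a baseline value is recorded before naming it.

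The cost is one replaced sentence and one added statement. No new data, visits or participants are needed.

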### Intervention

*Usual care cessation support:* Participants in both groups will receive usual care smoking cessation support, based on the Smoking Cessation Guidelines for Australian General Practice [11] This includes a quit pack (available from Quitline), which covers planning and preparing to quit, strategies for quit success, and coping with cravings. Participants will also be directed to other resources, including the ‘My QuitBuddy’ mobile app, and the web-based QuitCoach. These resources provide personalized quit plans, monitor progress and money saved, and motivation and support from others using the app. Participants will also be directed to call Quitline should they wish to speak to a counsellor about their quit attempt. Quitline is a confidential service with a professional advisor available for counseling and advice on quitting smoking.

*10,000 steps pedometer group:* participants assigned to this group will receive a resource pack and pedometer, and will be asked to increase their daily steps to 10,000. The resource pack contains a log-book to record steps/day, number of cigarettes smoked, and hints and tips for increasing step counts. The log-book is based on resources used by the Queensland 10,000 steps project (www.10000steps.org.au) Trained research staff will phone these participants once a week to check and record pedometer use and discuss barriers and strategies for successfully increasing PA.

*HIIT group:* participants assigned to this group will complete two gym-based supervised sessions (supervised by trained research staff) and one home-based HIIT session each week. The HIIT protocol will be completed by fast walking or running on a treadmill with the deck inclined to reach the desired intensity, or on a cycle ergometer if individuals are unable or do not wish to use the treadmill. The 35 min protocol consists of: warm-up at 65 % of heart rate maximum (HRmax) (5 min); 4 **×** 4 min intervals at 85–95 % HRmax (with the target zone reached by at least two minutes), interspersed with 3 min recovery at 65 % HRmax; and cool down (5 min), with a total exercise time of 35 min (see Fig. 2). Attendance at supervised sessions and adherence to home-based sessions (including compliance with target heart rate) will be monitored and recorded by research staff.

After the 12-week intervention researcher support will be removed from both groups (e.g. removal of supervised HIIT sessions and 10,000 steps support). Researcher contact will only be made to arrange and complete follow-up measures during weeks 13 and 26.

### Data collection

Participants will be assessed on three occasions: at baseline, week 13 and week 26 (see Fig. 1). Cigarettes per day will be measured weekly. Withdrawal symptoms, cigarette cravings and feelings of stress, will be monitored during the intervention. See Table 2 for full list of measures, and measurement time-points. Exercise and fitness measures will be completed by research staff whom will be blinded to participant group allocation.

**Table 2 Tab2:** Timeline for data collection

	Measurement time-point					
Measures	Baseline	Week 2	Week 4	Week 8	Week 13	Week 26
Cigarettes per day (weekly)						
Smoking cessation					X	X
Withdrawal symptoms	X	X	X	X	X	X
Cigarette cravings	X	X	X	X	X	X
Cigarette dependence	X				X	X
Subjective stress	X		X	X	X	X
Saliva cotinine	X				X	X
Cardiorespiratory fitness	X				X	X
Lung function	X				X	X
Body composition	X				X	X
Physical activity	X				X	X
Well-being	X				X	X
Motivation	X				X	X
Demographic information	X				X	X

### Smoking measures

*Smoking abstinence and cessation* will be assessed using the Russell Standard [12]. This includes self-reported ‘quitting’ (not smoking for two weeks) and expelled carbon monoxide concentration (Micro Smokerlyser; Pico simple, Harrietsham, UK) of less than 10 ppm (which reflects abstinence from smoking during the previous 24-h). *Saliva* will be collected by drooling into a 50 ml Falcon tube. The sample will be frozen and stored for analysis of cotinine, which is a metabolite of nicotine. *Self-reported number of cigarettes* smoked will be recorded each week. *Withdrawal symptoms* and *cravings* will be assessed using the Mood and Physical Symptoms Scale (MPSS) [13]. *Smoking dependency* will be assessed using the Fagerström Test for Nicotine Dependance (FTND) [14]. *Subjective stress* will be assessed using the 4-item Perceived Stress Scale (PSS) to monitor any changes associated with smoking reduction or increasing PA [15].

### Exercise, fitness and physical activity measures

*Cardiorespiratory fitness (VO2max)* will be assessed using a graded exercise test to exhaustion. We will analyse expired air using a metabolic system (Trueone 2400, Sandy, USA) to calculate the maximal rate of oxygen consumed and used during the test. We will monitor participants’ ECG (CASE, Milwaukee, USA) during and after the test. Maximal heart rate attained will be used to determine the training intensity for each participant. We will measure blood pressure prior to and during the test.

This fitness test will be completed on a treadmill (T2100, Little Chalfont, UK) or a cycle ergometer (Lode Excalibur Sport, Groningen, Netherlands) if individuals are unable or do not wish to use the treadmill. The treadmill test will use a ramp protocol where the inclination is constant (5.5 %) and the speed increased 0.5 km/h every minute, starting at 4 km/h. The cycle protocol includes a 2 **×** 4 min warm-up at 25 W and 50 W. The test starts at 50 W and increases by 25 W every minute. We will ask participants to refrain from smoking two hours before the test, and from drinking alcohol, or doing any vigorous or moderate intensity activities 12-h before the test.

*Lung function* will be assessed by forced vital capacity [FVC], forced expiratory volume in 1 s [FEV_1_] and FEV_1_/FVC ratio, using a Vitalograph (2150, Ennis, Ireland). We will ask participants to inhale completely and rapidly through the mouth (not the nose), then exhale maximally and forcefully, with their lips creating an airtight seal around the mouthpiece, until no more air can be expelled (minimum of six seconds). Participants will repeat the manoeuvre three times, with a rest period of ≥1 min between efforts. Peak expiratory flow rate [PEFR]) will be assessed using a portable peak flow meter (Assess, Cedar Grove, USA), using the same technique as described above. Participants will repeat the manoeuvre three times, with a rest period of ≥1 min between efforts.

*Body composition* will be assessed by researcher measured body mass index (height, weight), and waist circumference. Standing height and weight will be measured using a stadiometer (SECA [contact], Hamburg, Germany) and electronic scale (Charder MS 3200, Hamburg, Germany) respectively. Waist circumference will be measured using a tape passed around the narrowest point of the abdomen. We will take each measure twice and use the average measure obtained, unless the first and second measures vary by more than 1 %, in which case we will use the median of three measurements. Body mass index will be calculated as weight (kg)/height^2^ (m^2^).

*Physical activity and sedentary time* will be measured using a wrist-worn GENEActiv accelerometer, which will be worn for one week at each measurement time. The GENEActiv is a tri-axial, ± 6 g seismic acceleration sensor. It is small (36x30x12 cm), lightweight (16 g), waterproof, and offers a near body temperature sensor to help improve the confirmation of wear and non-time. GENEActivs will be configured with a sampling frequency of 80 Hz, with data uploaded and converted to 15 s epoch .csv files using GENEActiv PC software version 2.1. We will import the epoch files into custom built Excel spreadsheets that will compute the most likely posture (lying, sitting, standing, ambulation), activity intensity (sedentary, light, moderate, vigorous) and sleep. This will provide information on average daily sedentary, active and sleep patterning and behaviour, and will provide a measure of overall weekly physical activity. GENEActiv validity studies have demonstrated strong correlations for criterion validity (r = 0.79 to 0.98) for physical activity and sedentary behaviour [5, 6]. Data in this study will be based on standard criteria for wear time [7].

